### Statistical analysis

Descriptive statistics will be used to report feasibility outcomes. Mean (SD) scores and mean differences (95% CI) will be used to explore differences in continuous variables between the groups and Cohen’s *d* will be calculated to evaluate efficacy for the secondary outcome measures. A small effect size (Cohen’s *d* ≥ 0.20) will be regarded as an acceptable between group difference to signal efficacy. Data that is not continuous (adverse effects and use of cointerventions) will be reported using frequencies, medians and interquartile ranges as appropriate. Between group differences will be explored using risk ratios. Missing data will be minimised as much as possible, however no statistical approaches will be used to replace missing data. Any missing data will be evaluated and reported.

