Recognising the critical role of patient-centred multidisciplinary team care in managing foot-related symptoms for individuals with rheumatological conditions, the need for universally accessible, publicly-funded podiatry services is clear. At present, access to podiatric care is largely restricted to the private sector, creating a significant barrier to equitable health provision. This study aims to assess the feasibility of implementing a pragmatic randomised trial to evaluate the effectiveness and cost-effectiveness of a publicly-funded podiatry service tailored for people suffering from foot-related symptoms due to rheumatological conditions. Furthermore, the study will explore patient-centred goal-setting as an outcome measure and obtain data to inform sample size calculations for a randomised trial.

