## Methods

This will be a pragmatic, participant-blind, parallel-group, randomised feasibility trial comparing access to a podiatry service with usual care. The trial is registered with the Australian and New Zealand Clinical Trial Registry (ANZCTRN12625001000493) and has been developed in accordance with the SPIRIT 2025 statement [17], the CONSORT 2010 statement extension to randomised pilot and feasibility trials [18], and the TIDieR checklist for reporting of interventions [19]. Ethics approval has been obtained from the La Trobe University Human Ethics Committee (Approval number HEC25095 on the 20th of May 2025) and written informed consent will be obtained from all participants during the baseline assessment.

The randomisation module in REDCap (Research Electronic Data Capture, Vanderbilt University, USA) will be used to randomise participants. Participants will be allocated on a 1 to 1 ratio with blocking in groups of 4 and 6, and stratification based on sex at birth to ensure a balance of participant sex between the groups. Allocation will be concealed from all researchers until after eligibility screening. Participants will be randomised to their intervention after completing consent at the baseline assessment.

Given this is a feasibility trial, only participants will be blind to their allocation. Both groups will be blind to group allocation through limited disclosure. All participants will be informed that two different types of treatment are being compared, however only the intervention group will be informed about the additional access to podiatry treatment.

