### Patient and public involvement

Recognising the importance of designing patient-centred research, we included a consumer as a coauthor (KL) during the initial design of the trial and securing grant funding. To further inform the trial design, we conducted four semi-structured interviews with people who have a rheumatological condition and foot-specific complaints. These interviews aimed to gather detailed feedback on various aspects of the trial, including the acceptability of the intervention, the feasibility of the proposed procedures, potential barriers to participation, and what outcomes are important. The interviews were conducted prior to the approval of the ethics application.

Participants will be recruited from outpatient rheumatology clinics at Austin Health in Melbourne, Australia. Rheumatologists will be informed about the trial and asked to recommend that their patients consider participating if they have foot-specific symptoms. Therefore, rheumatologists will initially approach participants about participating in the study and recommend that potential participants contact the researchers via a website. To be eligible for inclusion, participants must:be adults over 18 years of age;have a diagnosis of a rheumatological condition from a rheumatologist;have foot-specific symptoms rated 3/10 or greater on a numerical rating scale (e.g. pain, stiffness, dermatological complaints); andhave experienced symptoms for at least four weeks.

Participants will be excluded if they:are unable to understand the English language in verbal or written form;have regularly attended a podiatry service for management of their rheumatological foot problem in the past 3 months;have an active bacterial infection of the foot; andexperience foot symptoms that are not related to the rheumatological condition.

The recommended sample size for feasibility studies is 12 people per group [21], however to allow for a 20% drop-out rate, we will recruit 15 participants per group. This is similar to the median sample size of 30 for pilot trials documented in the United Kingdom Clinical Research Network database [22]. Given the low-risk nature of the interventions, we are not specifying interim analyses or guidelines for stopping the trial.

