### Other variables: limited efficacy testing

In addition to evaluating feasibility, limited efficacy testing will be undertaken on measures to be included in a fully powered randomised trial. These measures are outlined briefly in Table 2 and in specific detail in Online Resources 2.

**Table 2 Tab2:** Other variables measured for limited efficacy testing

Variable	Outcome measure	Timepoints
Goal attainment	Goal Attainment Scaling	Baseline and week 12
Global change	Global Perceived Rating of Change (15-point Likert scale)	Week 6 and week 12
	Patient Global Assessment	Baseline, week 6 and week 12
Foot-specific pain	Foot Health Status Questionnaire—foot pain domain	Baseline, week 6 and week 12
	Manchester-Oxford Foot Questionnaire—foot pain subscale	Baseline, week 6 and week 12
Foot-specific function	Foot Health Status Questionnaire—foot function domain	Baseline, week 6 and week 12
	Manchester-Oxford Foot Questionnaire—walking/standing subscale	Baseline, week 6 and week 12
Disability	Health Assessment Questionnaire—disability index	Baseline, week 6 and week 12
Stiffness	11-point numerical rating scale	Baseline, week 6 and week 12
Fatigue	Functional Assessment of Chronic Illness Therapy-Fatigue (FACIT-Fatigue) version 4	Baseline, week 6 and week 12
Change in physical activity	Global Physical Activity Questionnaire	Baseline, week 6 and week 12

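### Between-group differences and Cohen's d are planned without adjustment for baseline score or sex, and without saying whether follow-up or change scores are compared, which gives up precision that the collected data could provide

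*Protocol article*

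**What the plan says.** For continuous outcomes, the Statistical analysis section of the protocol article states: "Mean (SD) scores and mean differences (95% CI) will be used to explore differences in continuous variables between the groups". Cohen's d is then computed for the secondary measures, and a value of 0.20 or more "will be regarded as an acceptable between group difference to signal efficacy". No model or covariate is named. The section does not say whether the difference is between follow-up scores or between changes from baseline, nor which SD is the denominator of d. Missing values are not imputed.

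Three other places bear on this.

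- **Table 2 (Other variables: limited efficacy testing).** Nine of the 11 measures have the schedule "Baseline, week 6 and week 12". The Global Perceived Rating of Change has no baseline. Goal Attainment Scaling is listed at baseline and week 12, and the Procedures section says that what is entered for it at week 12 is the change.
- **Methods.** "Participants will be allocated on a 1 to 1 ratio with blocking in groups of 4 and 6, and stratification based on sex at birth".
- **Introduction.** One purpose of the study is to "obtain data to inform sample size calculations for a randomised trial".

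The sample size text, under Patient and public involvement, reads "The recommended sample size for feasibility studies is 12 people per group", and then "to allow for a 20% drop-out rate, we will recruit 15 participants per group".

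**The concern.** The trial collects a baseline value for most of its efficacy measures and stratifies by sex, yet the stated estimator uses neither. In groups this small, the two arms will often differ at baseline by chance. If follow-up scores are compared, part of that difference passes into the estimated effect. The efficacy signal is set at only 0.20 SD, so the part passed on can be as large as the signal.

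Two things are at stake. First, the estimates and intervals are wider than they need to be. Second, the study is meant to supply planning values for a larger trial. If that trial adjusts for baseline, it needs the residual SD or the baseline-to-follow-up correlation, and raw SDs alone do not give these.

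Leaving open follow-up versus change scores adds a smaller problem: the meaning of d = 0.20 depends on the score and the SD used.

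**Working it through.** **Inputs.** From the protocol article: 12 per group as the target, 20% drop-out, 15 per group recruited, no imputation, threshold d = 0.20. Assumed, because the article does not give it: a baseline-to-follow-up correlation r of 0.3, 0.5 or 0.7, with the same SD at both times. All results are in SD units. Probabilities use the normal approximation.

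**The plan's own figure.** 12 / (1 - 0.20) = 15 per group, 30 in total. This reproduces. The number analysed per group therefore lies between 12 and 15.

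**Chance baseline difference.** SE = sqrt(2/n): sqrt(2/12) = 0.408 and sqrt(2/15) = 0.365.

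**Part carried into an unadjusted follow-up d.** Only r times the baseline difference carries over, so its SD is r × sqrt(2/n). The probability that it reaches 0.20 in either direction is 2 × [1 - Φ(0.20 / (r × sqrt(2/n)))]. For example, at n = 15 and r = 0.5 the carried SD is 0.5 × 0.365 = 0.183, and 0.20/0.183 = 1.10, which gives 0.27.

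| r | Baseline difference needed (0.20/r) | Carried SD, n = 15 | Probability, n = 15 | Carried SD, n = 12 | Probability, n = 12 |
|---|---|---|---|---|---|
| 0.3 | 0.67 | 0.11 | 0.07 | 0.12 | 0.10 |
| 0.5 | 0.40 | 0.18 | 0.27 | 0.20 | 0.33 |
| 0.7 | 0.29 | 0.26 | 0.43 | 0.29 | 0.48 |

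**Standard error under three estimators.** Follow-up: sqrt(2/n). Change: sqrt(4(1 - r)/n). Baseline-adjusted: sqrt(2(1 - r²)/n).

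| r | Follow-up, n = 12 | Change, n = 12 | Adjusted, n = 12 | Adjusted, n = 15 |
|---|---|---|---|---|
| 0.3 | 0.408 | 0.483 | 0.389 | 0.348 |
| 0.5 | 0.408 | 0.408 | 0.354 | 0.316 |
| 0.7 | 0.408 | 0.316 | 0.292 | 0.261 |

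Adjustment is the most precise of the three at each correlation shown. With 12 per group, the 95% interval half-width falls from 0.85 SD (t on 22 df) to about 0.74 (r = 0.5) or 0.61 (r = 0.7). These formulas ignore the small cost of estimating the slope. A simulation with 40,000 replicates, adjusting for baseline only, gave adjusted standard errors of 0.362 and 0.299 at n = 12 for r = 0.5 and 0.7, against 0.354 and 0.292 by formula.

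**What 0.20 means under each denominator.** The SD of change is sqrt(2(1 - r)), which at r = 0.7 is 0.775. A d of 0.20 on that scale is 0.20 × 0.775 = 0.155 raw SD. Dividing an adjusted difference by the residual SD would inflate d by 1/sqrt(1 - r²), which is 1.15 at r = 0.5 and 1.40 at r = 0.7.

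**The threshold after adjustment.** With no true effect, the probability that d reaches 0.20 in favour of podiatry is as follows.

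| n per group | Unadjusted follow-up | Adjusted, r = 0.5 | Adjusted, r = 0.7 |
|---|---|---|---|
| 12 | 0.31 | 0.29 | 0.25 |
| 15 | 0.29 | 0.26 | 0.22 |

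**The case against.** **Nothing here is biased.** Under randomisation the unadjusted difference is unbiased, and its 95% interval already includes the variation from chance baseline imbalance. This stands: the point is about precision, in a 30-person feasibility study whose efficacy testing is described as limited.

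**The article may simply be silent.** Covariates are often left to an analysis plan, and none is shown. This stands in part. A reader might infer that the trial will compare raw follow-up scores and has decided to disregard baseline. The text says neither, and Goal Attainment Scaling is recorded as change. But the section does fix the estimator, the effect size, the threshold and the handling of missing data, and a plain mean difference is its natural reading. Reading it as a change score does not remove the point, because adjustment is at least as precise as either.

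**The imbalance can be overstated.** The baseline difference itself exceeds 0.20 SD with probability 0.58 (n = 15) to 0.62 (n = 12), and a reader might take that as the chance that d moves by 0.20. It is not, since only r times the difference carries over. At r = 0.3 the chance is at most 0.10.

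**Sex.** A reader might infer that leaving sex out of the analysis could also move d by 0.20. Stratified blocks already limit sex imbalance, so the omission costs a little precision and makes the interval slightly conservative.

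**Planning values.** The candidate primary outcome of the larger trial is Goal Attainment Scaling, which is entered as change. The residual-SD argument does not reach it, and the article does not say that the larger trial will adjust for baseline. Both stand, so this benefit is limited to the nine measures with a baseline score.

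**Conclusion.** The point holds as a low-cost improvement to the analysis. It is not an error that invalidates the plan. The stated comparison is unbiased but, for nine of the 11 measures, less precise than the collected data allow. It also leaves the score and the SD behind d undefined.

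If follow-up scores are compared, chance baseline imbalance alone shifts d by 0.20 or more with probability about 0.07-0.10, 0.27-0.33 or 0.43-0.48 at r = 0.3, 0.5 or 0.7. The concern is therefore material for correlations of about 0.5 or more and small at 0.3. The standard error with 12 per group falls from 0.41 to 0.39, 0.35 or 0.29 SD. These sizes rest on the assumed correlations, equal SDs at both times and 12 to 15 analysed per group.

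It would go too far to conclude that adjustment rescues the efficacy signal. With no true effect, d would still reach 0.20 by chance about 22-29% of the time at r = 0.5 to 0.7.

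**What to change.** - Estimate each mean difference (95% CI) by linear regression on group, the baseline value of that measure, and sex.
- For the Global Perceived Rating of Change and for Goal Attainment Scaling (recorded as change), adjust for sex only.
- Compute d as the adjusted difference divided by the pooled raw SD, not the residual SD, so that 0.20 keeps its meaning.
- For the measures with a baseline score, report the baseline-to-week-12 correlation and the residual SD beside the raw SD, to inform the sample size of the larger trial.

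The change is to wording only and needs no new data. It costs two degrees of freedom (22 to 20 with 24 analysed), or one where only sex is added. Most of the gain comes from the baseline term, and sex adds little. How far d of 0.20 can be relied on as a signal needs separate consideration.

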## Abstract

People with rheumatological conditions often experience debilitating foot-related symptoms requiring expert multidisciplinary care. However, in Australia there is a glaring gap in the provision of universally accessible, publicly-funded podiatry services. This study aims to assess the feasibility of a randomised trial evaluating a publicly-funded podiatry service for people with foot-specific symptoms related to rheumatological conditions. A pragmatic, participant-blind, parallel-group, randomised feasibility trial will compare effectiveness of a podiatry service with usual care. Consumer interviews will inform the design of the feasibility trial. Thirty adults with a rheumatological condition and foot specific symptoms will be recruited from an outpatient rheumatology clinic and randomised to receive access to a podiatry service or a control group who will receive usual care. Outcome measures will be obtained at baseline, week 6 and week 12. Feasibility will be evaluated using a framework that includes 10 important domains of uncertainty in pragmatic feasibility trials. Secondary outcomes (such as Goal Attainment Scaling) will also be collected and effect sizes of between group differences calculated to signal efficacy. The study will explore the feasibility of conducting a fully powered randomised trial of the effectiveness of a podiatry service for people with a rheumatological condition and foot-specific symptoms. In addition, the trial will determine the feasibility of Goal Attainment Scaling as a primary outcome measure for this population.

Trial registration.

The trial is registered with the Australian and New Zealand Clinical Trial Registry (ANZCTRN12625001000493 on the 9th of September 2025).

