Treatment will be provided by a podiatrist with over 10 years of experience in clinical practice, who is endorsed to prescribe scheduled medicines, has undertaken further training in rheumatological conditions, and plays an active role in the Australian Rheumatology Association. For participants who require foot orthoses, Formthotics™ (Foot Science International, Christchurch, New Zealand) full length prefabricated foot orthoses will be provided. These are manufactured from a dual-density polyethylene closed cell foam that has a firm-density bottom layer (Shore-A durometer 50), and a soft-density top layer (Shore-A durometer 25). Participants will be provided the foot orthoses in accordance with the manufacturer’s instructions by selecting an appropriate size, heating the foot orthoses using a specifically designed machine from Foot Science International, placing them within the participants footwear, and asking participants to stand to allow the foot orthoses to mould to the contour of the foot. Adjustments to the foot orthoses will be made to ensure the participants agree they are comfortable. Participants who require footwear will be provided with a $250 discount from the cost of new footwear. The footwear will be agreed with the podiatrist and participants will be required to attend pre-arranged footwear suppliers to receive the discount. Advice provided to participants about footwear is included in Online Resource 1. All other treatment, such as skin or nail care, exercises, or other aids, will be provided in line with standard podiatry practice in Australia.

The control group will receive usual care plus a self-management package based on advice from Creaky Joints Australia (29 Tips from Podiatrists for Managing Arthritis Pain in Your Feet), which provides a range of education including regular self-inspection of feet, advice about exercising to reduce foot/ankle discomfort, selecting appropriate footwear, and the use of supportive aids such as foot orthoses, ice packs, salt baths etc. For usual care, participants will be advised they can seek any treatment they prefer over the 12-week duration of the trial and their progress will be monitored. At the conclusion of the trial, participants randomised to the control group will be invited to attend a debriefing session and will be offered the same treatment as the intervention group if the intervention is found to be effective.

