### Main outcome variable: feasibility

Given this is a pragmatic trial, the framework developed by Chan et al. [23] will be used to determine feasibility. According to this framework, 10 important domains of uncertainty should be addressed in a pragmatic feasibility trial. These domains are outlined in Table 1 along with criteria that will determine whether a larger trial is feasible. In addition to the feasibility outcomes, data will be collected on participant characteristics, adherence to interventions, adverse effects and acceptability and credibility of the interventions. These outcomes are outlined in detail in Online Resource 2.

**Table 1 Tab1:** Domains and criteria used to evaluate trial feasibility

Domains of uncertainty	Criteria
1. Intervention development	No significant barriers to implementation of interventions are identified
2. Research ethics	No concerns are identified by the ethics committee
3. Participant identification and eligibility	There is a conversion rate of at least 75% (i.e. at least 75% of people screened are enrolled in the trial)
4. Recruitment	At least 5 participants are recruited per month
5. Setting	At least 60% of participants are recruited from rheumatology departments located in hospitals in northern Melbourne, Australia
6. Organisation	Resources required for the trial do not exceed the budget
7. Flexibility of delivery	There are minimal deviations from how interventions are delivered in clinical practice
8. Flexibility of adherence	The median self-reported adherence to the intervention is at least 3 ‘Sometimes’ on a Likert scale from 1, ‘Strongly disagree’ to 5 ‘Strongly agree’
9. Follow-up	Questionnaire completion rates at weeks 6 and 12 are at least 75%
10. Primary outcome	Semi-structured consumer interviews identify goal attainment as the most important outcome

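### An observed Cohen's d of 0.20 or more is taken to signal efficacy, but at 12 to 15 per group an ineffective service reaches that mark about 29 to 31% of the time on each outcome

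*Protocol article*

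**What the plan says.** The protocol article fixes a threshold for reading the secondary outcomes. Under Statistical analysis, Cohen's d is to be calculated to evaluate efficacy, and a d of at least 0.20 "will be regarded as an acceptable between group difference to signal efficacy". The Abstract repeats the purpose: "effect sizes of between group differences calculated to signal efficacy". The threshold applies to the point estimate. No confidence limit enters it, no error rate is attached, and no outcome or timepoint is singled out.

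The sample size is given under Patient and public involvement: "The recommended sample size for feasibility studies is 12 people per group", and "to allow for a 20% drop-out rate", "we will recruit 15 participants per group". Missing values will not be replaced.

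Two other parts of the article limit the role of the rule. Table 1, under Main outcome variable: feasibility, lists ten criteria for whether a larger trial is feasible, and none uses d. The Statistical analysis section also plans mean differences with 95% confidence intervals.

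Under Study groups, control participants "will be offered the same treatment as the intervention group if the intervention is found to be effective".

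**The concern.** A cut-off on an observed effect is useful only if it tends to separate a service that works from one that does not. With 12 to 15 people per group, the sampling error of d is about twice the cut-off, so an ineffective service will often pass on chance alone and a truly small effect will often fail.

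What is at stake is the statement the trial will make. Because the rule is prespecified, a chance difference of 0.20 standard deviations would be reported as a signal of efficacy with the authority of a planned criterion, even when its own confidence interval runs from appreciable harm to large benefit. With many outcomes and no statement of which should count, there are many chances for this to happen.

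**Working it through.** **Inputs from the protocol article**
- Threshold: observed d ≥ 0.20 (Statistical analysis).
- Group size: 15 recruited, 12 after 20% drop-out (Patient and public involvement); 1:1 allocation (Methods); no imputation (Statistical analysis).
- Comparisons: Table 2 lists 11 measures. Goal Attainment Scaling has one post-baseline timepoint (week 12) and the other ten have two (weeks 6 and 12), so 1 + 10 × 2 = 21.

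**Assumptions.** Roughly normal outcomes, equal variances, unadjusted comparison, and a signal counted only when it favours podiatry. No standard deviation is needed because d is standardised.

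**The plan's own figure.** 12 / (1 − 0.20) = 15 per group, which reproduces the stated recruitment target. The article states no error rate for the d rule, so there is nothing further to reproduce.

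**Precision of d.** Near zero, SE(d) = √(2/n).
- n = 12: √(2/12) = 0.408; 0.20 / 0.408 = 0.49 standard errors.
- n = 15: √(2/15) = 0.365; 0.20 / 0.365 = 0.55 standard errors.

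**Chance of meeting the mark on one outcome.** With no true effect this is P(T ≥ 0.20/SE) on 2n − 2 degrees of freedom. For other true effects it is the non-central t tail with non-centrality (true d)/SE.

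| True d | n = 12 per group | n = 15 per group |
|---|---|---|
| −0.20 | 16.6% | 13.8% |
| 0 | 31.5% | 29.4% |
| 0.20 | 50.2% | 50.2% |
| 0.50 | 77.0% | 79.5% |

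The null rate is robust. The normal approximation gives 31.2% and 29.2%, and the Hedges small-sample correction gives 30.8% and 28.9%. The article does not mention baseline adjustment; if it were used with an assumed baseline correlation of 0.3 to 0.7, the rate would be about 22 to 30%.

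**Interval around a just-passing result.** With variance 2/n + d²/(4n), an observed d of 0.20 has an approximate 95% interval of −0.60 to 1.00 at n = 12 and −0.52 to 0.92 at n = 15.

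**At least one false signal among 21 comparisons.** The article gives no correlations between outcomes, so a common correlation ρ is assumed and varied. With c the normal quantile matching the per-outcome rate above (0.483 at n = 12, 0.541 at n = 15), the probability is 1 − ∫ φ(z) Φ((c − √ρ z)/√(1 − ρ))²¹ dz.

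| Assumed ρ | n = 15 | n = 12 |
|---|---|---|
| 0.5 | 84% | 86% |
| 0.7 | 71% | 73% |
| 0.9 | 52% | 55% |

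**The case against.** The strongest reply is that little hangs on the rule. Table 1 sets the criteria for a larger trial, and d is not among them. The article calls the exercise limited efficacy testing and plans confidence intervals for the mean differences, so a reader would see the imprecision. The rule also carries some information, since it passes 77 to 80% of the time at a true d of 0.5. All of this stands, and it lowers the severity. It does not rescue the rule: the pass mark takes no account of the interval, and the article itself fixes both the number and the label, so this is not a detail left to a fuller document.

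Several stronger readings are tempting but unsupported:
- **A false signal is almost certain.** At a correlation of 0.9 the chance is only 52 to 55%, and high correlations are plausible when Table 2 pairs two pain scales and two function scales and repeats them in the same people. The calculation also counts any single pass, and the article states no such overall rule; the mark reads as applying outcome by outcome.
- **The rule ignores direction.** In ordinary reading a signal of efficacy means benefit, so a two-directional false-signal rate is not the relevant figure.
- **The later trial will be sized on d = 0.20 or on the observed d.** The article says only that data will inform the sample size. A projection of the larger trial's size or duration from 0.20 would answer a plan that is not stated.
- **The d rule decides what controls are offered.** Nothing in the article ties the offer under Study groups to the threshold.

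**Conclusion.** The threshold is wrong as written: it cannot do what its label claims. Each ineffective outcome has a 29 to 31% chance of being called a signal, against about 50% for a true effect equal to the threshold, a ratio of about 1.6 to 1.7. The rule is weakly informative rather than pure noise.

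The per-outcome figures follow from the article's sample size and the usual normal, equal-variance assumptions. The statement that at least one false signal is more likely than not rests further on an assumed common correlation of up to 0.9 and on counting any pass among the 21 comparisons.

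Severity is moderate. The analysis is secondary and exploratory, intervals on mean differences are already planned, and progression does not depend on d.

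The offer to controls is a separate wording point. It is conditional on a finding of effectiveness that a feasibility trial of this size cannot establish, whatever is done about the threshold.

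**What to change.** - In the Abstract and Statistical analysis, delete the d ≥ 0.20 pass mark and the wording about signalling efficacy.
- Report each mean difference and each d with its 95% confidence interval, described as estimates for planning only, with signs aligned so that a positive value favours podiatry on every scale. Intervals for the mean differences are already planned; extending them to d is the addition.
- State that no conclusion about efficacy will be drawn from this trial.
- Separately, reconcile the conditional offer under Study groups with a feasibility design that cannot determine effectiveness. How the offer should read is for the sponsor and investigators.

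The cost is wording only: no extra participants, visits or data, and the feasibility aims and Table 1 are untouched. The sponsor gives up the ability to claim a signal of efficacy from this trial.

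### For uncommon adverse effects, the risk ratio alone is a poor between-group measure at 12 to 15 participants per arm

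*Protocol article*

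**What the plan says.** The Statistical analysis section of the protocol article treats two variables as non-continuous: "Data that is not continuous (adverse effects and use of cointerventions) will be reported using frequencies, medians and interquartile ranges as appropriate". The next sentence gives the comparison between arms: "Between group differences will be explored using risk ratios". No second effect measure is named for these variables, and nothing is said about empty cells. For continuous outcomes the same section plans mean differences with 95% confidence intervals.

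The sample size is given under Patient and public involvement. The target is stated as "The recommended sample size for feasibility studies is 12 people per group" and then raised: "to allow for a 20% drop-out rate, we will recruit 15 participants per group". Allocation is 1:1 (Methods). The Statistical analysis section also says that missing values will not be replaced, so the number analysed per arm may be nearer 12 than 15.

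No adverse-effect rate is given anywhere. The only indication is qualitative: the sample-size paragraph describes the interventions as low-risk when it explains why there are no interim analyses or stopping guidelines.

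**The concern.** A risk ratio needs events in the control arm to be finite, and events in both arms to have the usual log-scale interval. At 12 to 15 per arm, an uncommon event can easily be absent from one arm or both. If the article's description of the interventions as low-risk means that particular adverse effects are uncommon, the named measure is weakest where the data are most likely to fall.

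What is at stake is modest but real. Adverse effects are among the data the trial sets out to collect (Main outcome variable: feasibility). Someone planning the larger trial would want to know what size of excess 30 people can and cannot rule out. An undefined ratio does not say this, whereas a risk difference with an interval does, even when both arms are empty.

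**Working it through.** **Inputs.** 12 per arm, 20% drop-out, 15 per arm (Patient and public involvement); 1:1 allocation (Methods); risk ratio as the between-group measure (Statistical analysis). The per-participant risk p over the trial is not in the article. It is assumed here, equal in both arms, at 5% to 30%. The ratio is taken as intervention over control; with equal risks, reversing it only swaps the two kinds of failure.

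**The plan's own figure.** 12 / (1 - 0.20) = 15 per arm, which matches the article.

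**Formulas.** Let q = (1 - p)^n be the chance that one arm of size n has no events.

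- Ratio infinite or 0/0 (control arm empty): q
- Ratio exactly 0 (only the intervention arm empty): q(1 - q)
- At least one arm empty: 1 - (1 - q)^2, the sum of the two lines above

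Worked case, p = 5% and n = 15: q = 0.95^15 = 0.463; q(1 - q) = 0.463 × 0.537 = 0.249; 1 - 0.537^2 = 0.712.

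| Risk p | n per arm | Control arm empty | Ratio exactly 0 | At least one arm empty |
|---|---|---|---|---|
| 5% | 15 | 0.463 | 0.249 | 0.712 |
| 5% | 12 | 0.540 | 0.248 | 0.789 |
| 10% | 15 | 0.206 | 0.163 | 0.369 |
| 10% | 12 | 0.282 | 0.203 | 0.485 |
| 20% | 15 | 0.035 | 0.034 | 0.069 |
| 20% | 12 | 0.069 | 0.064 | 0.133 |
| 30% | 15 | 0.005 | 0.005 | 0.009 |
| 30% | 12 | 0.014 | 0.014 | 0.027 |

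**Unequal risks.** With 5% in control and 20% in intervention, at least one arm is empty with probability 0.48 (n = 15) or 0.57 (n = 12). With 10% and 30%, the figures are 0.21 and 0.29.

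**What a continuity correction gives.** For 3/15 v 0/15, adding 0.5 to each cell gives (3.5/16) / (0.5/16) = 7.0. The standard error of the log ratio is √(1/3.5 - 1/16 + 1/0.5 - 1/16) = 1.47, so the 95% CI is 0.39 to 125.

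**What a risk difference gives (Newcombe, z² = 3.84).**

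- 0/15 v 0/15: the Wilson upper limit in each arm is 3.84 / (15 + 3.84) = 0.204. The difference is 0, with 95% CI -20 to +20 points.
- 3/15 v 0/15: the Wilson limits for 3/15 are 0.070 and 0.452; for 0/15 they are 0 and 0.204. The lower limit is 0.200 - √((0.200 - 0.070)² + 0.204²) = -0.04. The upper limit is 0.200 + (0.452 - 0.200) = 0.45. The difference is 20 points, with 95% CI -4 to 45.

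**The case against.** The strongest reply is that the size of the problem depends entirely on an event rate the article does not give. Calling the interventions low-risk is not a frequency, and it is said only to explain the absence of stopping guidelines. At a 20% risk an empty arm arises in 7-13% of trials, and at 30% in about 1-3%. The article also does not say whether the ratio is per type of event or for any adverse effect per participant. A pooled measure could nearly always be estimated. This stands, and it limits the point to individual or uncommon adverse effects.

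A reader might go further and infer that the between-group safety comparison as a whole will frequently give no usable estimate. The document does not support that, for three reasons. First, it would need a low event rate that is nowhere stated. Second, a ratio of 0 is still a point estimate, and only its log-scale interval fails; at n = 15 the ratio itself is infinite or undefined in 46% of trials at a 5% risk and 21% at 10%, below the 71% and 37% for any empty arm. Third, frequencies per arm are planned in any case, so 0/15 v 0/15 would be visible to every reader.

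Nor can the point be extended to co-interventions. Under Study groups, usual-care participants are told they are free to seek other treatment during the trial, and nothing suggests that such use will be rare.

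Finally, rules for empty cells are often left to an analysis plan, and the article refers detail on adverse effects to Online Resource 2; neither is shown. The absence of such a rule is therefore not the finding. What remains is the choice the article does state: the ratio as the only between-group measure named.

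**Conclusion.** The point holds as a minor one. The only between-group measure named for adverse effects gives no log-scale interval, and often no finite estimate, when the effect is uncommon. At 12 to 15 per arm and a risk of about 10% or less in both arms, at least one arm is empty in more than a third of trials (37-49% at 10%, 71-79% at 5%). At 20% the difficulty is occasional and at 30% it is rare.

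These figures rest on an assumed, equal, per-participant risk and on independence between participants. The article supplies the arm sizes but not the risk.

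The consequence is small. The comparison is exploratory, none of the ten criteria in Table 1 depends on it, and no stopping guideline uses it.

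**What to change.** In the Statistical analysis section, keep the planned frequencies and add that between-group differences in adverse effects will be given as risk differences with a small-sample 95% CI (Newcombe or Miettinen-Nurminen), with risk ratios reported only where both arms have events. Risk ratios may stay as they are for co-intervention use. This also brings adverse effects into line with the mean differences and 95% confidence intervals already planned for continuous outcomes.

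The cost is one sentence of text and no extra data. The drawback is that the intervals will be wide, as the -20 to +20 points for two empty arms of 15 shows. That width reflects what a trial of 30 can say about uncommon harms.
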